### Data collection and analysis plan

2.4

#### Baseline data

2.4.1

At enrolment, baseline demographic data and relevant clinical data about the course of the disease and treatment to date are retrieved from medical records and documented. These include date of diagnosis, localization and pathology of the primary tumor and of recurrences/distant metastases, previous and current therapies, and current disease stage and symptoms.

Study data are collected and managed using the Research Electronic Data Capture (REDCap) tool hosted at the Medical Center - University of Freiburg, Germany (33, 34). REDCap is a secure, web-based software platform designed to support data capture for research studies, providing (1) an intuitive interface for validated data capture; (2) audit trails for tracking data manipulation and export procedures; (3) automated export procedures for data downloads to statistical packages; and (4) procedures for data integration and interoperability with external sources (33, 34). Study records are pseudonymized and access to identifying information of the participants is strictly limited. Data will be retained for 10 years in accordance with policy.

#### Local clinical and histological tumor response

2.4.2

The primary outcome of the HISTOTHERM study is the evaluation of local clinical and histological tumor response. Clinical tumor response is evaluated guided by the assessments defined by RECIST; notably complete response (disappearance of target lesion), partial response (>30% decrease), stable disease (< 30% decrease, <20% increase) and progressive disease (>20% increase) of the treated tumor (35). Since imaging diagnostics (CT/MRT) is not indicated as a standard therapy control during course of the treatment, treatment response is evaluated according to the investigator’s assessment. Clinical evaluation includes optical control, photographic documentation and palpation and is done during treatment and at follow-up visits six weeks after end of treatment followed by three-months intervals for the initial year and six-months intervals thereafter, for a cumulative duration of five years. Local clinical response is reported as discrete data (36).

Pathological regression is evaluated on Hematoxylin-Eosin (H&E) stained slides with Cytokeratin stained sections as reference according to the grading system of Miller-Payne in pre- and post-treatment samples (37). Frequency distribution and descriptive statistics are employed for the characterization of the treatment response. In order to compare molecular profiles and survival of different treatment responses, patients are grouped according to their clinical and histologic response. We will employ a generalized linear mixed model with Poisson distribution for evaluation.

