We will conduct a two-fold analysis of protein expression patterns, firstly focusing on alterations during the course of the treatment, and secondly comparing expression between patient groups displaying varying treatment responses. Histologic and clinical regression will be statistically correlated with the histopathologic findings. In pursuit of predictive histologic markers for therapy response, we will perform rate modeling using Poisson regression with offset and exploratory factor analysis. Cluster analysis will be employed to identify relevant biological processes in the tissue. The identified proteins and processes will lay the foundation for further investigations for therapy prediction.

Further, mass spectrometry-based proteomics is used to identify proteome alteration from the limited biopsy material. Proteome profiling by liquid chromatography – tandem mass spectrometry is performed essentially as described in our recent benchmarking study (39). From the biopsies before and if applicable during treatment and from the primary diagnosis, 1-2 sections of 10 μm section thickness will be prepared for proteomic analysis after micro- or macrodissection and measured on a Q-Exactive+ high performance mass spectrometer. Due to the scarcity of sample material, we focus on abundance proteomics. Data-independent acquisition with label-free quantification will be used.

We expect a proteome coverage in excess of 3000 proteins measured in our micro- or macrodissected tissue slides. For analyses, we will consider proteogenomic probing of common genomic alterations. Statistical evaluation will involve supervised and unsupervised approaches. Hierarchical clustering will be employed to identify proteomic subgroups, and algorithms that are tolerant for a low frequency of missing values will be considered. Protein expression will be associated with outcome data using multivariate Cox-type analyses, including consideration of boosting steps if required. We will also consider multivariate linear models, as highlighted by linear models of microarray analysis, including consideration of variable selection by tools such as elastic nets. Multiple testing correction will be considered. The proteomic profiles will be correlated with treatment stage and success to identify potential protein markers indicating a particularly good or poor response.

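### Section 2.4.2 names only a Poisson mixed model, but the primary outcomes defined there are ordered categories and a grade, not counts

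*Protocol article*

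**What the plan says.** Section 2.4.2 (Local clinical and histological tumor response) states: "The primary outcome of the HISTOTHERM study is the evaluation of local clinical and histological tumor response". Clinical response takes one of four RECIST-guided values: complete response, partial response, stable disease or progressive disease. The investigator judges it repeatedly, during treatment and at follow-up visits. Histological response is a Miller-Payne grade.

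Three sentences on analysis follow, in this order:

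- The first is descriptive: "Frequency distribution and descriptive statistics are employed for the characterization of the treatment response".
- The second turns response into a grouping factor, so that molecular profiles and survival can be set against each other across response groups.
- The third names the model: "We will employ a generalized linear mixed model with Poisson distribution for evaluation".

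The section does not say what the Poisson model is fitted to, how the categories or grades are coded, or whether there is an offset or a robust variance. Section 2.4.3 makes a separate Poisson statement about histologic markers: "we will perform rate modeling using Poisson regression with offset and exploratory factor analysis". Section 2.4.5 gives survival its own methods: Kaplan-Meier plots, log-rank tests and Cox regression. Section 2.5 sets 40 patients on pragmatic grounds and gives no response rate, significance level or power.

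**The concern.** A Poisson model is meant for counts and takes the variance to equal the mean. An ordered four-level response, a bounded regression grade and a yes/no complete response are not counts, and their variance generally differs from their mean. When the variance is below the mean, the mixed-model part does not help, because a random effect can only add variance.

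Any standard error, interval or test that this model produced for the primary outcome would then be miscalibrated. The direction would depend on how the categories happen to be numbered. With 40 patients, intervals that are needlessly wide could hide real differences, and intervals that are too narrow could suggest differences that are not there. The article states this method for the primary outcome, so it is not a detail left open for a later plan.

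**Working it through.** **Inputs.** From the document: four ordered categories and a regression grade (section 2.4.2), and n = 40 (section 2.5). There is no plan figure to reproduce, because the document states no response rate, standard error, significance level or power for this outcome. All response distributions below are therefore assumptions. Miller-Payne is taken as graded 1 to 5, also an assumption, since the article does not give the number of grades.

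**Formula.** Ratio of the Poisson model-based standard error to the true one = sqrt(mean / variance). Above 1 means too wide, below 1 too narrow.

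**Yes/no response.** The mean is p and the variance p(1-p), so the ratio is 1/sqrt(1-p).

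| p (assumed) | ratio |
|---|---|
| 0.1 | 1.05 |
| 0.3 | 1.20 |
| 0.5 | 1.41 |
| 0.8 | 2.24 |

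**95% half-widths at n = 40.** Binomial: 1.96 × sqrt(p(1-p)/40). Poisson: 1.96 × sqrt(p/40).

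- p = 0.3: 0.142 against 0.170.
- p = 0.6: 0.152 against 0.240.
- p = 0.8: 0.124 against 0.277. The Poisson upper limit is 0.8 + 0.277 = 1.08, or 1.13 if formed on the log scale, so it is not a possible response rate.

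**Scored clinical categories.** Take 60/25/10/5% for complete/partial/stable/progressive. The variance is 0.74 under every coding below, but the mean moves with the coding:

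- Complete = 4 down to progressive = 1: mean 3.4, sqrt(3.4/0.74) = 2.14.
- Complete = 1 up to progressive = 4: mean 1.6, ratio 1.47.
- Complete = 3 down to progressive = 0: mean 2.4, ratio 1.80.
- Complete = 0 up to progressive = 3: mean 0.6, ratio 0.90.

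Over five assumed distributions the ratio runs from 1.12 to 2.41 for scores 1 to 4, from 1.01 to 2.06 for scores 0 to 3 with complete = 3, and from 0.75 to 1.11 with complete = 0.

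**Regression grade 1 to 5.** The ratio is 1.22 for a uniform distribution, 1.58 for a central one, 1.64 for mostly high grades, 0.95 for a polarised one and 0.87 when all patients sit at the two ends.

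**Type I error at a nominal 5%.** Simulation of two groups of 20, 3,000 runs, Wald test on the log rate ratio, no random effect:

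- Yes/no response: 0.7% at p = 0.3 and 0.1% at p = 0.6.
- Scores 1 to 4, 60% complete responses: 0.0% to 0.2%.
- Grade 1 to 5, mostly high: 0.2%. Polarised: 6.5%.
- Scores 0 to 3 with complete = 0: 7.2% (60% complete), 10.2% (polarised) and 10.9% (80% complete).

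In the last group the variance exceeds the mean. A random effect can absorb some of that excess, so 7% to 11% describes the model without one.

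**A use in which Poisson is correct.** For an example table of category counts (12, 5, 2, 1 against 6, 6, 5, 3), the Poisson log-linear deviance is 4.505 and the multinomial likelihood-ratio statistic is also 4.505. Applied to cell frequencies, the Poisson model has no variance error.

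**The case against.** The strongest reply is that the article never says the response is the dependent variable. The Poisson sentence comes directly after the one that makes response a grouping factor, so response could be the predictor. The study also has genuine counts: section 2.4.3 counts stained cells and structures. A log-linear model of category frequencies would be valid, as shown above. This stands as a limit on certainty, but it does not clear the text. Section 2.4.2 defines no count, and the Poisson regression for histologic markers is stated separately in section 2.4.3. A mixed model also points to repeated values per patient rather than an aggregated table. On any of these readings the sentence needs correcting or completing.

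A reader might infer that the error bars will be far too wide and that much power is lost. The document does not support that as a general result. At response rates of 10% to 30% the excess is only 5% to 20%, and some codings make the intervals too narrow. Large power losses can be produced: for 20 against 20 patients, 80% against 45% gives 16% power with Poisson and 65% with a binomial score test, and 65% against 30% gives 28% and 59%. But these rates and the even split are invented for a non-randomised study without a control arm, and they assume model-based variance. With a robust variance the Poisson comparison has 59% and 57%, so most of the loss goes.

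It is also fair that the study is exploratory, states no primary hypothesis test, and reports response by frequencies that the model does not touch. That lowers the severity.

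**Conclusion.** The point holds in a limited form. The one model named for the primary outcome does not fit the outcomes defined in the same section, and nothing stated there (count, offset or robust variance) would make it fit. If it is fitted to those outcomes, the standard error is about 0.75 to 2.4 times the correct one over the scored-category distributions tried. For a yes/no response it is 1.05 to 2.24 times the correct one for rates of 10% to 80%. The error is usually conservative but not always.

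These sizes rest on assumed response rates, codings and number of grades, and on a two-group comparison without a random effect. Neither the direction nor the size can be derived from the document itself. A reader might also take the grouping sentence to mean that survival is to be analysed with Poisson. Section 2.4.5 already assigns survival its own methods, so this calls for a cross-reference only. Severity: moderate.

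**What to change.** In section 2.4.2, name the dependent variable and replace the Poisson model for response:

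- **Clinical response category (repeated) and regression grade:** a cumulative-logit (ordinal) mixed model with a patient random intercept.
- **Complete response yes/no:** logistic regression, or Poisson regression with a robust variance if a rate ratio is wanted, with exact (Clopper-Pearson) intervals for the response rates.
- **If the Poisson model was meant for cell counts:** say so and move the sentence to section 2.4.3, beside the Poisson regression with offset.
- **Survival by response group:** refer to the Kaplan-Meier, log-rank and Cox methods already in section 2.4.5.

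The cost is analysis-plan wording only. The patients, visits, biopsies and collected data stay the same.

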#### Identification of predictive markers and affected histological and cellular processes

2.4.3

Our overarching objective involves the discernment of tumor characteristics and the elucidation of a mechanistic basis underpinning responses to or resistance against the therapeutic intervention. Therefore, secondary outcomes of the HISTOTHERM study are the characterization of histologic and cellular differences within subgroups of patients to determine markers and key regulated processes involved in or activated by the combination therapy. To achieve these goals, comprehensive immunohistological and proteomic analyses on tissue and blood-based analyses will be undertaken.

Residual diagnostic tissue samples collected pre-treatment, during treatment (dose of 12 Gy) and at follow-up are used for analyses. Where available, tissue from the primary diagnosis is included in the analysis. Biopsies are routinely paraffin-fixed and embedded, followed by cutting of all required sections. After completion of routine diagnostics, study-specific immunohistochemical staining will be carried out on Formalin-fixed Paraffin Embedded (FFPE) tissue by trained staff of the CCCF biobank to obtain a comprehensive picture of the core processes involved.

Among the principal foci of investigation are the regulatory dynamics of the immune system, the mechanisms underpinning apoptosis and senescence. Approximately 20 different antibodies will be deployed for immunostaining of key proteins involved in those processes. Immunostaining will be performed in a standardized manner on multiple samples in parallel and will always include positive and negative controls to identify confounding staining effects. Subsequently, sections will be digitized and electronically archived on internal servers for further analysis.

Histologic sections are analyzed by trained staff who are blinded to clinical outcome. Depending on the marker protein under investigation, we will quantify and evaluate staining pattern, tissue distribution, intensity and number of positive and negative cells. Image analysis is supported by digital analysis tools, such as QuPath, which was developed specifically for pathological analysis (38). The tissue separation and cell detection tools are used for image classification and quantification of staining intensity, percentage of positive and negative cells and antibody distribution. Positively stained tissue structures are counted manually.

We will conduct a two-fold analysis of protein expression patterns, firstly focusing on alterations during the course of the treatment, and secondly comparing expression between patient groups displaying varying treatment responses. Histologic and clinical regression will be statistically correlated with the histopathologic findings. In pursuit of predictive histologic markers for therapy response, we will perform rate modeling using Poisson regression with offset and exploratory factor analysis. Cluster analysis will be employed to identify relevant biological processes in the tissue. The identified proteins and processes will lay the foundation for further investigations for therapy prediction.

Further, mass spectrometry-based proteomics is used to identify proteome alteration from the limited biopsy material. Proteome profiling by liquid chromatography – tandem mass spectrometry is performed essentially as described in our recent benchmarking study (39). From the biopsies before and if applicable during treatment and from the primary diagnosis, 1-2 sections of 10 μm section thickness will be prepared for proteomic analysis after micro- or macrodissection and measured on a Q-Exactive+ high performance mass spectrometer. Due to the scarcity of sample material, we focus on abundance proteomics. Data-independent acquisition with label-free quantification will be used.

We expect a proteome coverage in excess of 3000 proteins measured in our micro- or macrodissected tissue slides. For analyses, we will consider proteogenomic probing of common genomic alterations. Statistical evaluation will involve supervised and unsupervised approaches. Hierarchical clustering will be employed to identify proteomic subgroups, and algorithms that are tolerant for a low frequency of missing values will be considered. Protein expression will be associated with outcome data using multivariate Cox-type analyses, including consideration of boosting steps if required. We will also consider multivariate linear models, as highlighted by linear models of microarray analysis, including consideration of variable selection by tools such as elastic nets. Multiple testing correction will be considered. The proteomic profiles will be correlated with treatment stage and success to identify potential protein markers indicating a particularly good or poor response.

In order to identify systemic immunologic processes, EDTA blood (2 x 9 ml) will be collected from patients at the indicated time points for measurement of exosomal Hsp70 (40, 41) in the plasma, for enumeration of circulating tumor cells (40, 42, 43), and for a phenotypic characterization of lymphocyte subpopulations.

The major stress-inducible Hsp70 which is overexpressed in many highly aggressive tumor cells and metastases (44), promotes tumor growth due to its cytoprotective capacity (45). Tumor cells with a high Hsp70 expression frequently present Hsp70 on their plasma membrane (46, 47) and actively release Hsp70 in extracellular vesicles such as exosomes (48, 49). Therefore, Hsp70 will be measured in the blood of patients in the course of therapy by using the compHsp70 ELISA (40) which is able to quantify vesicular and free Hsp70. In contrast, normal cells contain Hsp70 in the cytosol but do not present it on the plasma membrane (50, 51). High levels of intra- and extracellular Hsp70 levels are associated with therapy resistance in different tumor types (52) and therefore, measurements of exosomal Hsp70 in the circulation during and after therapy might predict therapy response and can therefore be considered as a negative prognostic marker (44, 52).

The enumeration of circulating tumor cells (CTCs) which are considered as precursors of metastases are useful in predicting therapy resistance and overall survival in metastatic diseases (53) but a major limitation of this approach is the rarity of CTCs in the blood. Most antibody based selection approaches are based on antibodies directed against the epithelia cell adhesion molecule EpCAM (CD326) (54). However, it is known that following epithelial-to-mesenchymal transition (EMT) the expression of EpCAM is frequently downregulated on CTCs (55, 56), whereas the levels of membrane bound Hsp70 remains stably high (42, 57). Therefore, in this study we will comparatively examine the number of CTCs which are isolated on an EpCAM (epithelial CTCs) versus Hsp70 (epithelial and mesenchymal CTCs) antibody based bead approach in patients with advanced tumor disease in the course of therapy and in the follow-up period as a predictive marker for tumor aggressiveness and EMT.

Immunophenotyping of lymphocyte subpopulations in the peripheral blood will be performed to measure immunomodulatory activities of radiotherapy in combination with hyperthermia on the innate and adaptive immune system. It is well known that Hsp70 as one of the danger associated molecular patterns (DAMPs) can stimulate NK cell mediated immune responses (58). In a pilot study and in phase I and II clinical trials beneficial effects could be demonstrated by *ex vivo* Hsp70/IL-2 stimulated NK cells in patients with advanced colon and lung cancer (59–61). In this study we aim to measure the proportions of major lymphocyte subpopulations such as CD3+/CD4+ CD3+/CD8+ T helper and cytotoxic T lymphocytes, CD3+/CD94+ NK-like T cells, CD3+/CD4+/CD25+/FoxP3+ immunosuppressive T regulatory cells, CD19+ B cells, and CD3-/CD56+, CD94+, NKG2D+, NKp30+, NKp40+, CD69+ NK cell subpopulations in the course of therapy by multiparameter flow cytometry using fluorescence-labeled antibodies (59, 62). The aim is to identify an immune cell signature which might be able to predict clinical outcome.

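### Slide-reader blinding is stated for clinical outcome only, which leaves the first planned marker comparison, change across biopsy time points, without a stated safeguard against reader expectation

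*Protocol article*

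**What the plan says.** All of the following is in the protocol article.

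- **Blinding rule (section 2.4.3).** "Histologic sections are analyzed by trained staff who are blinded to clinical outcome". Nothing is added about biopsy time point, slide coding or reading order.
- **Material (section 2.4.3).** "Residual diagnostic tissue samples collected pre-treatment, during treatment (dose of 12 Gy) and at follow-up are used for analyses". Tissue from the primary diagnosis is added where available.
- **Planned comparisons (section 2.4.3).** Protein expression is analysed in two ways, "firstly focusing on alterations during the course of the treatment", and "secondly comparing expression between patient groups displaying varying treatment responses".
- **How sections are scored (section 2.4.3).** Depending on the marker, staff assess staining pattern, distribution, intensity and cell numbers. "Image analysis is supported by digital analysis tools, such as QuPath"; the software is listed as quantifying intensity, percentage of positive and negative cells, and distribution. The paragraph ends: "Positively stained tissue structures are counted manually".
- **Other safeguards.** Staining is standardised, is done on several samples in parallel, and "will always include positive and negative controls to identify confounding staining effects" (section 2.4.3). "Study records are pseudonymized and access to identifying information of the participants is strictly limited" (section 2.4.1).
- **Design and size.** There is no randomised control group (section 2.1). Enrolment is 40 patients, with about 20 antibodies (section 2.5).

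**The concern.** Blinding protects a comparison only if it hides the variable being compared. Hiding clinical outcome stops a reader from scoring responders differently from non-responders. It does not stop a reader from scoring a 12 Gy section differently from a pre-treatment section of the same patient. Yet that contrast is the one named first, and it bears directly on the secondary objective of finding processes activated by the combination therapy.

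The study is built on expectations about the direction of change, for instance in immune regulation and apoptosis. A reader who shares those expectations and can see the time point may shift counts or pattern scores slightly in one direction. Such a shift does not average out over patients. It adds to the within-patient difference and looks like an effect of treatment. With no untreated series biopsied on the same schedule, nothing in the slide data would separate a reading shift from a biological one. The article says that the identified proteins and processes will be the basis for later work on therapy prediction, so a spurious change could be carried forward.

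**Working it through.** **1. Reproduce the plan's own figure.** Section 2.5 counts three biopsies plus one tissue sample from primary diagnosis or recurrence, each stained with about 20 antibodies: (3 + 1) × 20 = 80 sections per patient, and 80 × 40 = 3200 in total. Both stated figures reproduce. The plan gives no alpha, effect size or power for the marker comparisons, so there is no further figure to check.

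**2. Set each comparison against each stated safeguard.**

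| Safeguard | Change over time points | Response groups |
|---|---|---|
| Readers blinded to clinical outcome | not covered | covered |
| Pseudonymised records | identity only; nothing on time-point labels | identity only |
| Parallel staining with controls | staining artefacts, not reader expectation | the same |
| Software quantification | reduces the risk for intensity, percentage positive and distribution | the same |
| Untreated control series | none | not needed for this bias |

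What remains open is reader-dependent scoring in the time-point comparison: manual counts of positive structures, and staining pattern, which is not among the listed software outputs.

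**3. Could a small shift matter at this sample size?** This step is illustration only. The documents give neither a shift, nor a within-patient correlation, nor a paired t-test.

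- Assumptions: no true change; a systematic reading shift δ between two time points, in SDs of the marker; within-patient correlation ρ = 0.5; two-sided 5% paired t-test; n = 40 complete pairs (all enrolled patients) or n = 30 (an assumed lower number of evaluable pairs).
- SD of the paired difference = √(2(1 − ρ)) = √(2 × 0.5) = 1. At ρ = 0.5 it therefore equals the marker SD.
- Non-centrality = δ / 1 × √n. For δ = 0.2 and n = 40: 0.2 × 6.325 = 1.265. For δ = 0.3 and n = 40: 0.3 × 6.325 = 1.897.
- The rejection probability comes from the non-central t distribution with n − 1 degrees of freedom.

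| Shift δ | n = 40 | n = 30 |
|---|---|---|
| 0 | 5% | 5% |
| 0.1 SD | 9.5% | 8.3% |
| 0.2 SD | about 23% | about 18% |
| 0.3 SD | about 46% | about 36% |
| 0.5 SD | about 87% | about 75% |

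A higher correlation makes the SD of the difference smaller and the rates higher; a lower correlation does the opposite. The table applies to one reader-scored marker. It must not be multiplied by 20, because the article does not say how many of the antibodies depend on manual counting.

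**The case against.** **Silence is not absence.** A reader might infer that the slide readers know the time point. The documents do not say so. They are silent on labels, coding and reading order, and a condensed article may leave such laboratory detail to the full protocol. This stands, and the point is therefore worded as masking not stated. It does not remove the point. The article does not leave blinding to another document: it states a rule, and that rule fits only one of the two comparisons named in the same section.

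**Much of the scoring is digital.** Intensity, percentage positive and distribution are listed as software outputs, and manual counting is stated only for positively stained structures. This stands and narrows the concern to part of the immunohistochemistry. A reader might infer that every one of about 20 markers is exposed; the article does not support that.

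**Slides are not the only evidence.** A reader might infer that the whole account of treatment-induced change rests on slide reading. It does not. Mass-spectrometry proteomics, plasma Hsp70, circulating tumour cells and lymphocyte phenotyping also follow patients over treatment, and slide scoring does not enter them.

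**The figures are assumed.** They are. The article names Poisson models, factor analysis and cluster analysis, not a paired t-test, and it gives no alpha. The table shows that a modest shift can matter with 40 pairs, not that one occurs.

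**Masking will be imperfect.** Treatment effects in the tissue may reveal the time point. This is true for some sections and is no reason to leave the others unmasked.

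**Severity.** These are secondary markers in an exploratory study. This stands and limits the rating.

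**Conclusion.** The point holds in a limited form. The stated blinding covers clinical outcome, so it protects the response-group comparison but not the comparison over time that is listed first, and no other stated safeguard closes that gap for manual counts and staining pattern. The possible consequence is a created or inflated apparent change over time in reader-scored immunohistochemistry, with no control series to expose it. It does not extend to the proteomic or blood-based results.

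The documents do not establish that readers see the time point, or that any treatment effect has been manufactured. The size is unknown. Under the stated assumptions (40 pairs, correlation 0.5, paired t-test, no true change), a shift of 0.2 SD gives about 23% false positives per marker instead of 5%, and 0.3 SD about 46%. Severity is moderate to low: a cheap improvement to a secondary, exploratory analysis.

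**What to change.** Amend the blinding sentence in section 2.4.3 so that readers of the study-specific sections are blinded to clinical outcome and biopsy time point. To carry this out:

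- give each digitised study-specific section a random code;
- read the sections in random order within each marker;
- unlock the codes only after the scores are entered.

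If the full protocol already provides this, one added clause settles the matter. Recruitment has run since 11/2019, and the article does not say whether sections have been read. For any already read without masking, state this as a limitation of the time-course results.

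Miller-Payne grading is exempt, because it needs the pre- and post-treatment samples side by side. Study-specific staining follows completion of routine diagnostics, so masking need not touch the diagnostic reading at 12 Gy.

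Cost: recoding files and a random reading list for sections that are to be digitised anyway, with no extra tissue, patients or readers. The downsides are minor logistics and incomplete masking where treatment effects are visible in the section.
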